## Abstract

Pain and knee stiffness are common problems following total knee replacement surgery, with 10–20% of patients reporting dissatisfaction following their procedure. A remote assessment of knee stiffness could improve outcomes through continuous monitoring, facilitating timely intervention. Using machine learning algorithms, computer vision can extract joint angles from video footage, offering a method to monitor knee range of motion in patients’ homes. This study outlines a protocol to provide proof of concept and validate a computer vision-based approach for measuring knee range of motion in individuals who have undergone total knee replacement. The study also explores the feasibility of integrating this technology into clinical practice, enhancing post-operative care. The study is divided into three components: carrying out focus groups, validating the computer vision-based software, and home testing. The focus groups will involve five people who underwent total knee replacement and ten healthcare professionals or carers who will discuss the deployment of the software in clinical settings. For the validation phase, 60 participants, including 30 patients who underwent total knee replacement surgery five to nine weeks prior and 30 healthy controls, will be recruited. The participants will perform five tasks, including the sit-to-stand test, where knee range of motion will be measured using computer vision-based markerless motion capture software, marker-based motion capture, and physiotherapy assessments. The accuracy and reliability of the software will be evaluated against these established methods. Participants will perform the sit-to-stand task at home. This will allow for a comparison between home-recorded and lab-based data. The findings from this study have the potential to significantly enhance the monitoring of knee stiffness following total knee replacement. By providing accurate, remote measurements and enabling the early detection of issues, this technology could facilitate timely referrals to non-surgical treatments, ultimately reducing the need for costly and invasive procedures to improve knee range of motion.

## 1. Introduction

Total knee replacement (TKR) is a common procedure, with over 100,000 operations performed annually in England and Wales [1]. While most patients experience successful outcomes following TKR, approximately 10–20% of patients are dissatisfied—primarily due to pain and knee stiffness [2]. A recent James Lind Alliance Priority Setting Partnership identified ways to understand the causes of knee stiffness after TKR, how it can be prevented, and the best treatments as a top-10 priority for clinical research [3]. A method to detect early problems with pain and stiffness could facilitate earlier referral to non-surgical treatments which are effective in preventing the need for more invasive treatments, such as manipulation under anaesthetic [4].

Our current understanding of the onset, timing, and optimal treatment for stiffness is limited. An accurate remote assessment of knee stiffness could improve outcomes through continuous monitoring and timely interventions. This will reduce the need for frequent clinic visits. Knee stiffness post-TKR is defined as range of motion (ROM) limitation and is often associated with pain [5,6]. ROM is typically measured using a handheld goniometer or through a visual assessment by a clinician. Both methods have been shown to be inaccurate [7]; therefore, a more precise method of measurement is required. Furthermore, these methods require trained healthcare staff, so they are impractical for remote assessment. Therefore, the ideal tool for measuring knee stiffness should be accurate, easy to use, and capable of providing rapid feedback to both patients and clinical teams.

Markerless pose estimation using computer vision has the potential to be used by patients to improve remote rehabilitation [8]. Computer vision is a branch of artificial intelligence that uses machine learning algorithms to automate the analysis of human movement from videos. A computer vision-based approach has been validated for the clinical assessment of spine mobility in patients with ankylosing spondylitis [9]. However, it is important to validate machine learning algorithms for the TKR population to account for individual differences in movement patterns. By providing accurate knee flexion measurements, computer vision could enhance the assessment of knee ROM and facilitate targeted interventions. This study aims to develop and validate a computer vision-based approach to monitor knee flexion and extension.

Functional tasks that reflect daily movements, such as the sit-to-stand task, could be used to monitor knee ROM. These tasks are easier to complete in the home environment than goniometer measurements and represent functional ability. The sit-to-stand test is recommended for monitoring recovery from TKR surgery [10]. Evidence suggests that sagittal plane knee ROM is decreased during the sit-to-stand task after TKR surgery compared to healthy controls [11], indicating that this task may be used to measure ROM in post-operative patients. Therefore, this study will use the sit-to-stand test to measure ROM in a home-based setting.

The computer vision-based approach offers a non-invasive, objective method to monitor knee flexion in patients with knee stiffness, which could inform treatment decisions to improve outcomes. Currently, no tool exists to remotely and accurately detect early post-surgical knee stiffness. This study seeks to develop a cost-effective tool for measuring and quantifying knee stiffness pre- and post-TKR surgery for use across the NHS. This study also aims to determine its reliability, feasibility, and usability for implementation in the home.

The primary objectives of the study are the following:To provide proof of concept for a computer vision-based approach that measures knee ROM for use in the home setting.To validate the computer vision-based approach in people who have undergone TKR by ascertaining the test–retest reliability of algorithm outputs such as knee flexion/extension angles.To investigate the integration of the computer vision-based approach into clinical practice through focus groups and identify key development areas for successful implementation.

The secondary objectives of the study are the following:To explore how pain influences knee ROM in people who undergone TKR.To investigate the relationship between muscle activation and ROM in people who have undergone TKR and in healthy controls.To describe the association between physical activity and ROM in people who have undergone TKR.To identify the potential risk factors, measured using questionnaires, linked with knee stiffness post-TKR surgery.

This study will be split into three stages: (1) focus groups, (2) validation of the computer vision-based approach for measuring knee range of motion in the laboratory, and (3) home testing. These will be outlined and addressed separately within the protocol.

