#### 2.2.4. Inclusion and Exclusion Criteria

Inclusion Criteria—Group of Participants who underwent TKR:Adults (aged 18 years and over);Individuals who have undergone total knee replacement in the past five to nine weeks.

Inclusion Criteria—Healthy Adult Group:Adults (aged 18 years and over);Participants with no previous musculoskeletal injuries (past six months) or current neuro-musculoskeletal disorders that affect standing and walking.

Exclusion Criteria:Individuals with cognitive impairment affecting their ability to participate and follow instructions safely;Individuals with any skin conditions or broken skin in the calf and behind the knee area;Individuals with deep brain stimulation or pacemaker implants or other implants that may interfere with the measurement system.

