### 4.2. Validation of Computer Vision-Based Approach

Participants will wear an activity monitoring accelerometer for one week before the experimental session at the university. The accelerometer will be removed at the session. Physical activity monitoring can be repeated in the week following the visit if there are any problems with the data.

Motion capture markers and sEMG electrodes will then be applied. A physiotherapist will administer questionnaires.

A static trial will be recorded, followed by a series of gait/functional tasks. Participants will complete a two-minute walk on a treadmill at a self-selected walking speed. A sit-to-stand test will then be completed three times: participants will start in a seated position and stand up, then sit down without the use of their hands.

Participants will then be asked to complete the timed-up-and-go test (TUG) three times. The participant will start by sitting down in a chair and will stand up, walk forward three metres, turn around a cone, and then walk back to the chair before sitting down. Finally, an overground walking task will be completed three times: the participant will be asked to walk five metres, turn around a cone, and walk another five metres.

Knee range of motion will be measured by a trained physiotherapist. The maximum and minimum angles will be measured using a universal goniometer whilst lying on a physiotherapy couch and whilst seated on a chair.

Participants will be offered the chance to rest between procedures for as long as preferred. The Single Ease Question (SEQ) is a concise post-task questionnaire utilising a seven-point rating scale to gauge the perception of the difficulty or ease of a specific task. The SEQ will be completed after every task. Following the completion of testing, all equipment will be removed from the participant.

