#### Data Analysis 

Descriptive and frequency statistics will be reported for demographic, usability, acceptability, and feasibility data, and missing data will be reported.

To validate the motion capture measurements of the computer vision-based motion capture software against those from the marker-based motion capture software, we will use Bland–Altman (Tukey mean-difference) plots to assess for systematic deviation and determine any necessary bias correction.

To determine the test–retest reliability of the motion capture knee ROM measurements and to identify potential risk factors associated with knee stiffness, we will apply mixed-effects linear models for knee ROM adjusted for the group (group that underwent TKR or control) and questionnaire scores, with random effects for each participant. Variance components of the mixed-effects model may be used to estimate reliability measures as follows:

Relative reliability will be estimated using the intra-class correlation (2) (ICC) of Two-Way Random Effects [24]. Interpretation of ICC values will be conducted according to published guidance: an ICC of less than 0.5 is considered poor, between 0.5 and 0.75 is moderate, between 0.75 and 0.90 is good, and above 0.90 is excellent [25]. Absolute reliability will be estimated by the standard error of measurement (SEM) [26], calculated as $SD\left(standard\;deviation\right)\times \surd (1-ICC)$. The Minimal Detectable Change at the 95% confidence level (${MDC}_{95}$) is the minimal amount of change that would be accepted as a real change greater than that seen due to random variation or error [26]. MDC_95_ is calculated as follows: ${MDC}_{95}=1.96\times SEM\times \sqrt{2}$.

To explore the relationship between knee ROM and pain, muscle activation, physical activity, and potential risk factors, appropriate correlations/statistical tests will be selected to describe associations.

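### Scores taken at the same postoperative visit as knee ROM can be reported as correlates of stiffness, but not as its potential risk factors

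*Protocol article*

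**What the plan says.** The secondary objectives in section 1 of the protocol article include "To identify the potential risk factors, measured using questionnaires, linked with knee stiffness post-TKR surgery" and "To explore how pain influences knee ROM in people who undergone TKR". Section 1 also fixes the outcome: "Knee stiffness post-TKR is defined as range of motion (ROM) limitation and is often associated with pain".

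The entry criterion for the patient group (section 2.2.4) is: "Individuals who have undergone total knee replacement in the past five to nine weeks". Section 4.2 describes one laboratory session. In it, "A physiotherapist will administer questionnaires", the motion-capture tasks are performed, and then "Knee range of motion will be measured by a trained physiotherapist".

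Section 3.2.2 lists seven questionnaires: a demographic form and six scored instruments (PROMIS-29, OKS, NRS pain, IPAQ short form, Barthel Index, EQ-5D-5L).

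The Data Analysis part of section 4.2 states the purpose of the model: "to identify potential risk factors associated with knee stiffness, we will apply mixed-effects linear models for knee ROM", adjusted for group and questionnaire scores with a random effect per participant. A later sentence there says that correlations or other tests will be chosen to describe associations of ROM with pain, muscle activation, physical activity and potential risk factors.

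**The concern.** A risk factor has to come before the outcome. Here the explanatory scores and the outcome are recorded on the same day, weeks after surgery, and nothing is recorded beforehand. Most of the scored instruments describe present or recent pain, function, activity or health status, and a knee that does not bend can worsen all of these. A patient may have a low OKS because the knee is stiff, yet the plan would list that score as a candidate risk factor for the stiffness.

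What is at stake is the conclusion of one secondary objective, and the directional wording of a second. Section 1 itself presents the causes of stiffness after TKR as a research priority, so readers are likely to take a list of risk factors seriously.

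**Working it through.** **1. Timing of each measurement**

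- *Surgery:* five to nine weeks before participation (sections 2.2.2 and 2.2.4).
- *Questionnaires:* at the laboratory session (section 4.2).
- *Laboratory ROM, by motion capture and goniometer:* at the same session (section 4.2).
- *Accelerometry:* "Participants will wear an activity monitoring accelerometer for one week before the experimental session at the university", or the week after if there are data problems. For an eligible patient this is also postoperative.
- *Later contact:* home video and the System Usability Scale, to be completed within a week of the visit (section 4.3).
- *Before surgery:* nothing is planned.

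That the scores are collected once is inferred from the single session; no repeat is stated.

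**2. What the scores measure**

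From section 3.2.2: the OKS covers pain and function; the NRS, pain; the IPAQ, activity over the last seven days; the Barthel Index, personal care and mobility; the EQ-5D-5L, mobility, usual activities and pain among its dimensions; PROMIS-29, physical and mental health. The outcome is ROM that day, which section 1 says often goes with pain. Only the demographic form holds items that can predate surgery, such as age, sex, ethnicity, smoking and other medical conditions.

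**3. Whether the analysis can tell direction**

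For one score and ROM with sample correlation r, the test statistic is

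t = r × √((n − 2) / (1 − r²)).

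Swapping score and ROM leaves r, and so t, unchanged. With covariates in a linear model, r becomes a partial correlation, which is also symmetric.

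A simulation with n = 30 and 20,000 replicates bears this out. The share of samples significant at two-sided 5% was 0.61, 0.83 and 0.96 at true correlations of 0.4, 0.5 and 0.6. It was identical whether ROM drove the score or the score drove ROM.

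**4. How often a pure consequence would be flagged (illustration only)**

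The protocol gives no score–ROM correlation, so a range is assumed. The protocol's one power figure, Table 1, is reproduced first to fix the convention. A two-sided two-sample t-test at 5% with 30 per group gives 0.119, 0.208, 0.332, 0.478, 0.628, 0.760, 0.861, 0.929 and 0.968 for effect sizes 0.2 to 1.0. This agrees with the table to two decimals.

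For a correlation ρ, Fisher's approximation gives power ≈ Φ(atanh(ρ) × √(n − 3) − 1.96).

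- ρ = 0.5, n = 30: 0.549 × √27 = 2.85; Φ(2.85 − 1.96) = 0.81.
- ρ = 0.5, n = 20: 0.549 × √17 = 2.26; Φ(2.26 − 1.96) = 0.62.

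| Assumed ρ | n = 30 | n = 20 |
|---|---|---|
| 0.3 | 0.36 | 0.25 |
| 0.4 | 0.60 | 0.42 |
| 0.5 | 0.81 | 0.62 |
| 0.6 | 0.95 | 0.82 |

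Here n = 30 is the planned TKR group, and n = 20 assumes that the 40 complete cases in section 2.2.2 split evenly between groups. These values are the power to detect one unadjusted correlation of the assumed size. They do not measure reverse causation. They show that a score which is purely a consequence of ROM could well reach significance, and that a larger sample raises that chance without saying anything about direction.

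**The case against.** The strongest reply is that the protocol already claims little. The objective speaks of factors that are potential and linked, the last sentence of Data Analysis promises only to describe associations, and sections 2.2.3 and 5.2 call the research exploratory. That sentence also lists pain and physical activity apart from potential risk factors, and section 1 gives each its own objective; the one for activity is worded as an association. This much stands. The point is therefore firmest for the function and health-status scores. For pain it rests mainly on the word *influences* and on pain being one of the questionnaire scores. The hedges convey uncertainty, however. They do not tell the reader that direction cannot be identified, and section 5.2 names selection bias and generalisability but not cross-sectional timing.

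Several stronger readings are tempting, and the document does not support them:

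- *That factors predating surgery are left out of the objective.* Section 3.2.2 counts the demographic form among the seven questionnaires and says that it includes clinical scores and comorbidities, so age, sex, smoking and comorbidities fall within an objective measured by questionnaire.
- *That every score is taken after stiffness began.* No onset date is given, and section 1 says onset and timing are poorly understood. Only postoperative, concurrent measurement is established.
- *That the scores would be used to select patients for treatment.* No questionnaire-based selection or prediction rule is planned. The personalised thresholds discussed in section 5 are linked to collected data and to ROM or other kinematic variables.

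Nor is this a detail to leave to a statistical analysis plan: no analysis can recover temporal order from scores taken at the same visit.

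**Conclusion.** The point holds as one of labelling and inference. With concurrent measurement and no preoperative values, the planned model cannot distinguish a potential risk factor from a consequence of restricted ROM for any of the six scored instruments. Restricting the model to TKR patients would not cure this. The conclusion rests on the timing in sections 2.2.4 and 4.2 and does not depend on the assumed correlations.

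A reader might go further and infer that consequences of stiffness *will* be published as its risk factors. The hedged wording and the separate treatment of pain and activity do not support that certainty.

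The matter should be corrected, but it is confined to one secondary, exploratory objective and the phrasing of another. The validation and reliability objectives and Table 1 are not touched.

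**What to change.** 1. In the secondary objectives and in Data Analysis, reserve the term potential risk factors for characteristics that predate surgery and are already on the demographic questionnaire: age, sex, ethnicity, smoking and comorbidities. Include drug history only if it is recorded as preoperative. Name these explicitly as the candidates in the model.
2. Report OKS, PROMIS-29, EQ-5D-5L, Barthel, NRS and IPAQ at five to nine weeks as cross-sectional correlates of ROM.
3. Reword the pain objective as the association between concurrent pain and knee ROM.
4. Add to section 5.2 that scores and ROM are measured at one visit, so the direction of any association cannot be determined.

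The cost is a narrower claim with fewer candidate risk factors. No figure, study procedure or sample size changes.

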## 2. Experimental Design

This project will be underpinned by the new Medical Research Council guidelines for developing a complex intervention [12]. It will use a participatory design methodology that uses evidence-based research and behaviour change models to identify intrinsic and extrinsic factors that contribute to a given outcome in a specific population.

### 2.1. Focus Groups

Focus groups will be conducted with people who have undergone TKR surgery (*n* = 5) and healthcare professionals and carers (*n* = 10). Discussions will provide valuable insights into the future adoption and application of the computer vision-based approach.

Staff involved in rehabilitation or care provision (clinicians, carers, and managers; *n* = 10) will be convened to discuss how the computer vision-based approach will be deployed. We will identify barriers and facilitators to deployment and report how these should be addressed.

People who have undergone TKR surgery (*n* = 5) will explore potential issues that may be experienced when using the system in their homes. We will explore support structures (e.g., social networks) and barriers/facilitators to engagement. Potential software, hardware, support, and training changes will be mapped and reported. Patient/carer instruction materials will be created.

A final service and product specification, including reference to the materials above, will be prepared to inform the second stage of this study.

#### 2.1.1. Inclusion and Exclusion Criteria

The inclusion criteria are as follows:People aged ≥18 years old;People who have undergone total knee replacement surgery or those who have worked with people following this surgery as a clinician, carer, or therapist;Individuals who are able to give informed consent;Individuals who are able to communicate in English with the research team.

The exclusion criteria are as follows:Individuals with any medical condition compromising their safety or ability to take part in the study;Individuals unable to adhere to the study procedures.

#### 2.1.2. Sampling Technique

Convenience sampling will be used to recruit healthcare professionals/carers and people who have undergone TKR surgery. Convenience sampling is appropriate because the research is exploratory in nature. The research team will identify them through professional networks and associations to invite them to take part in the study. Participants who underwent TKR surgery will be identified through participant engagement groups.

### 2.2. Validation of Computer Vision-Based Approach

#### 2.2.1. Study Setting

This study will be conducted at the University of Exeter’s Richards Building, St Luke’s Campus. Participants will be recruited from the Princess Elizabeth Orthopaedic Centre based at the Royal Devon and Exeter, the Nightingale Hospital Exeter, and the North Devon District Hospital.

#### 2.2.2. Sample Size

Sixty participants (thirty participants who underwent total knee surgery five to nine weeks prior and thirty healthy controls) will be recruited for the project. Formal sample size estimates are not required for pilot and feasibility studies (PAFs). The choice of sample size (60 participants, 40 with complete data) reflects a balance between a large enough sample to represent population diversity and provide estimates of variability while ensuring that recruitment is achievable (participant drop-out and approximately 50% of eligible participants recruited). While there are no specific recommendations for sample sizes for PAFS, a general rule of thumb suggests a minimum of 30 people [13]. Twenty to thirty people are generally sufficient to estimate the standard deviation of outcome measures to estimate the sample size for a definitive clinical trial based on known estimates of Minimal Clinically Important Differences [14].

For the chosen sample size of 30 participants in each group, the power to detect varying effect sizes at a statistical significance level of 5% is shown in Table 1.

